### Promoting adherence and retention

To promote retention and reduce the incidence of dropouts over the 12-month follow-up period, the intervention coordinator will remain in close contact with the participants and be available by phone to discuss potential issues. The team will also contact participants in advance of their 12-month follow-up assessments. Participants who withdraw from the study will be invited to attend their follow-up assessments.

### Primary outcome measures

#### Feasibility: recruitment, adherence, retention

i)Recruitment.

A research coordinator will be responsible for logging recruitment activities as participants contact the study email or phone number. The research coordinator will document the following information of each participant: name, phone number, email, date of first contact, how they heard of the study, and whether they passed telephone screening. For participants that pass initial screening, they will be scheduled to meet with an assessor for a second screening and to provide consent. Upon completing the second screening session, the research coordinator will document whether they passed or failed screening. Recruitment feasibility will be determined by the average number of participants recruited per month (target: ≥ 9 participants per month).

ii)Adherence.

Instructors will keep a detailed attendance record for each component of each session (EX/STRETCH and DIET/ED). The target is ≥ 75% of EX and ≥ 75% of DIET sessions completed [66]. Adherence will be measured through subjective participation scores that are completed by the instructor and volunteer of each session, as well as by self-reported RPE ratings provided each session by participants in the EX groups. For each EX/STRETCH and DIET/ED component, participants will be confidentially scored on a scale from 1 to 3. A score of 3 indicates that the participant actively followed along with all exercises/stretches or DIET/ED content and participated in exercises/stretches or listened or contributed greater than 80% of the session. A score of 2 indicates that a participant engaged/contributed to 50–80% of the session and a 1 indicates that a participant engaged in less than 50% of the session. Self-reported attendance records for the independent sessions will also be collected, noting RPE rating (for EX groups), and any symptoms experienced during EX and STRETCH. For diet quality specifically, adherence will be measured through adherence to the Brain Health Food Guide recommendations and will be assessed using the Eating Pattern Self-Assessment (EPSA) [54].

iii)Retention.

Patients will be considered “non-completers” upon confirmation from a participant that they no longer wish to participate or are unable to participate. When a participant drops out of the study, the instructor will inform the research coordinator who will document withdrawals. The research coordinator will categorize reasons for non-completion as medical or non-medical. The feasibility target for retention is defined as ≥ 80% of participants with complete 6-month assessments.

### Secondary outcome measures

Each participant will complete two assessments at baseline (t_1_), post-intervention (t_2_), and 6 months post-intervention (t_3_) (see Fig. 1 for overview). All assessments will take place over Zoom® with a research assistant or coordinator who is blinded to group allocation.

At virtual assessment 1 (55 min), the following will be assessed: (1) Demographics: age, sex, gender, race and ethnic origins, education, marital status, type of residence, geography of residence (urban/rural), socioeconomic status; (2) Medical and mental health history and current use of medications; (3) Technology proficiency assessed using 10 questions adapted from AGE-WELL’s Canadian Attitudes toward Technology and Aging Questionnaire [67]; (4) Functional strength assessed with the 5-time sit-to-stand test, which is a validated test of lower body function and strength among older adults [68]. The participant will be timed as they stand from a seated position 5 times using a chair of standard height (same chair at each assessment); (5) Physical activity assessed using the Physical Activity Scale for the Elderly (PASE) which is valid among older adults aged 65–100 years and will be used to characterize habitual physical activity, and maintenance of physical activity levels during the post-intervention period [69]; (6) Health-related quality of life (QOL) measured using the SF-36 questionnaire [70], which will be used to develop weightings for quality-adjusted life-years (for the full-scale trial). The SF-36 also includes 8-scale scores that can be grouped into physical health QOL and mental health QOL. The SF-36 has been shown to be a valid and practical instrument to assess the quality of life of older adults living at home [71]; (7) Psychological health including depressive symptoms measured using the Center for Epidemiological Studies-Depression scale (CES-D) [72] and perceived anxiety measured using the Geriatric Anxiety Inventory (GAI) [73]. The CES-D has demonstrated high validity and reliability among older adults [72, 74]. The GAI has demonstrated a strong ability to identify geriatric anxiety, with studies reporting a high internal consistency and validity of the questionnaire [73, 75]; (8) Waist circumference assessed as a simple indicator of vascular risk [76]. The assessor will oversee the measurement, ensuring the tape measure is in the correct position. This measurement will be taken a second time to ensure accuracy, with both values will be recorded and an average of both values being used; (9) Diet quality measured using the Eating Pattern Self-Assessment (EPSA) which collects self-reported intake of the 15 targeted food items from the BHFG. In addition to t_1_, t_2_, and t_3_, the EPSA will also be administered monthly to participants in the DIET group to help with goal setting, while it will be administered mid-way through the program for participants in the ED groups. At post-intervention, participants will complete a survey to gather feedback about their experience in the program.

At virtual assessment 2 (30 min), executive function will be assessed by a composite measure of executive function, consisting of the Cambridge Brain Sciences (CBS) Double Trouble (Stroop), Monkey Ladder (visuospatial working memory), and Feature Match (attention speed) tasks [77]. Memory will be assessed by delayed recall on the Rey Auditory Verbal Learning Test (RAVLT) [78] and the CBS Paired Associates task [77]. These tests were chosen as they measure the cognitive domains of interest and have been validated for remote delivery [79–81].

### Sample size

A recent meta-analysis of exercise on cognition found Cohen’s *d* effect sizes between 0.27 and 0.36, dependent on combinations of exercise mode, frequency, duration, and outcome [16]. Effect sizes for diet interventions are highly variable depending on the intensity of the intervention. The most similar published diet intervention was in a factorial RCT of exercise and diet (without a goal-setting component) that found an effect size of 0.32 for exercise and 0.30 for diet [82]. The intensity of the current study intervention is higher than in this prior study, and it is expected that the goal-setting will increase adherence. However, virtual delivery may weaken adherence. As a result, an effect size of 0.30 was chosen for sample size estimates for the full-scale trial.

For the full-scale trial, it is estimated that 88 participants are needed per intervention arm (total of 364 participants) to detect EX (*d* = 0.3) and DIET (*d* = 0.3) effects with an alpha level of 5% and 80% power. With 10% dropout, 404 participants are needed for a full-scale trial over 3.5 years. As a result, for this feasibility trial, 140 participants will be recruited over 1.25 years to test the feasibility of the rate of recruitment that would be required for the full trial. Interim analysis of feasibility will be performed after the first three waves complete the 6-month assessment.

This sample size should also be appropriate for measuring feasibility outcomes. To confirm the sample size was sufficient, we considered a study adherence as a dichotomous outcome with a binomial distribution, where each participant will either complete the 6-month assessment (1) or not (0). With a sample size of 140, anticipated adherence of 80% can be estimated to within a 95% confidence interval from 72% to 86%.

### Data handling

Investigators and study staff will collect only the information needed for this study. Data will be stored in password protected files on computers, and in locked rooms. Data related to questionnaires will be collected using Qualtrics software (August 2023) and stored on an encrypted drive. All personal identifying information will be removed from the data and will be replaced with an ID code. Following completion of the study, data will be made available on an open science platform (platform yet to be determined, with participant consent) so that other researchers will have the opportunity to validate and replicate the results. All data shared in an open science framework will be de-identified and only study staff will be able to link this data to any personal identifying information.

For the memory and learning tests, there may be audio recordings to ensure that the researcher scores the test results accurately. These tests will also be saved with an ID code so that names cannot be identified and they will be stored until data analysis is complete.

### Safety and monitoring procedures of adverse events

To minimize the risk of adverse events, individuals must be screened safe to participate in moderate exercise using the CSEP Get Active Questionnaire [50] or have physician approval to engage in moderate intensity exercise without in-person supervision. The risk of adverse events is minimized by having exercise prescription completed by a CEP, by monitoring symptoms at each session, and through appropriate emergency protocols. Procedures are in place to monitor adverse events that participants may experience during the intervention. Grading and categorization of adverse events will be conducted using the Common Terminology Criteria for Adverse Events [83]. Participants will be queried about adverse events at each session and study visit. In situations where a participant reports exercise-related changes, such as muscle soreness and joint pain, the CEP will meet with the participant individually to gain further information about the changes. The CEP will determine whether the participant is safe to continue to exercise (although with modifications) or whether they should seek further medical attention. If a participant is deemed not safe to continue exercising, the CEP will follow-up with the participant weekly to determine when it is safe for them to re-join (if necessary, study physicians will be consulted in this process). For all adverse events that occur during the study, research staff are instructed to contact the University of Waterloo and Baycrest Research Ethics Boards. Adverse events for this study are defined as any undesirable experience that occurs to a participant during the 6-month intervention, regardless of whether they are perceived to be related to the intervention, and whether they are an expected consequence of the intervention. For adverse events that occur which are perceived to be related to the intervention, study physicians will be alerted. If it is unclear whether an adverse event is study related, the event and the conditions will be shared with study physicians.

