### Analysis

Analysis of primary objectives related to feasibility outcomes will be descriptive. “Success” will be based on predetermined criteria outlined in “Objectives and hypothesis” which included: (1) Recruitment: ≥ 9 participants/month over 1.25 years; (2) Adherence: (a) ≥ 75% of Aerobic and Resistance Exercise (EX) sessions and ≥ 75% of Diet Counseling (DIET) sessions are completed; (b) improvement in diet quality at 6 months compared to baseline; (3) Retention: ≥ 80% of randomized participants complete the 6-month assessment of executive function. Overall, “success” will indicate that the protocol is adequately robust to proceed to a large RCT with small or no adaptations, and failure to meet these targets indicating a need for substantial change before proceeding. Preliminary analyses of feasibility outcomes will be conducted at the end of year 2 by an independent statistician when the first three waves complete their 6-month assessment. If the data support feasibility, the research team will apply for funding to roll directly into the definitive trial.

Full analyses will be conducted once all participants have completed their 12-month follow-up assessments. Analyses will explore whether feasibility outcomes vary by gender as research suggests that exercise and diet preferences vary by gender [45, 84]. Feasibility outcomes will be described among women and men, and among non-binary and other gender groups if possible. Analyses will also explore whether other demographics, geographical location, or technology access predict adherence. Characteristics of the participants who withdraw and reasons for withdrawal will be analyzed and intent-to-treat analyses will be used. Individuals who withdraw from the study will be invited to take part in post-intervention and 6-month post-intervention assessments and a sensitivity analysis will be completed. In addition, effect sizes for EX and DIET will be determined for the future, full-scale trial by gender. An analysis of effect sizes will be conducted from both intention-to-treat and per protocol analyses (to understand potential effectiveness in relation to adherence).

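### Routine adverse-event enquiry is tied to sessions and study visits, so participants who stop attending without being judged unsafe may be under-asked and the recorded harm rate may be too low

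*Protocol article*

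**What the plan says.** All of the following is in the protocol article.

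- **Definition.** The section on safety and monitoring procedures counts "any undesirable experience that occurs to a participant during the 6-month intervention", whether or not it is related or expected. Attendance is not a condition.
- **Routine enquiry.** The same section states: "Participants will be queried about adverse events at each session and study visit".
- **People stopped for safety.** Someone who reports an exercise-related change is seen individually by the exercise physiologist. The section continues: "If a participant is deemed not safe to continue exercising, the CEP will follow-up with the participant weekly".
- **Withdrawal.** Under Promoting adherence and retention, "Participants who withdraw from the study will be invited to attend their follow-up assessments". The Analysis section says the same: "Individuals who withdraw from the study will be invited to take part in post-intervention and 6-month post-intervention assessments".
- **Reason for leaving.** Under the retention outcome, "The research coordinator will categorize reasons for non-completion as medical or non-medical". Non-completer status depends on the participant confirming that they will not or cannot continue.
- **Other contact.** Under Promoting adherence and retention, "the intervention coordinator will remain in close contact with the participants and be available by phone to discuss potential issues". The team also contacts participants ahead of the 12-month assessment.
- **Other records.** Symptoms in independent sessions are self-reported (adherence outcome). Medical history and medications are repeated at both follow-up time points (Table 1).

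**The concern.** The definition is unconditional, but the stated enquiry depends on taking part. If attendance were unrelated to harm, this would cost only some events. It is plausibly related: participants are aged 65 to 85, have low activity levels, and exercise at home without in-person supervision, partly in an unsupervised weekly hour. Pain, injury or illness are ordinary reasons to stop joining.

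The loss could also differ between arms. EX is progressed in difficulty and STRETCH is not, so both the reasons for stopping and the frequency of stopping may differ. At stake is the harm profile that the pilot passes on to the planned 404-participant trial, and the collection rule itself, which would carry over if the pilot is judged successful with few adaptations.

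**Working it through.** **1. Which stated routes reach a person who stops attending without reporting a problem?**

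| Route | Reaches this person? |
|---|---|
| Question at each session | No, once they no longer join |
| Self-reported symptoms in independent sessions | Not if they stop those as well |
| Weekly follow-up by the exercise physiologist | No; it starts only after someone is judged unsafe to continue |
| Coordinator contact | Possibly, but no adverse-event question is attached to it |
| Medical or non-medical reason for leaving | Only if withdrawal is confirmed; the article does not say whether a harm given as the reason is also graded |
| 6-month visit | If they accept; recall of up to 6 months |
| 12-month visit | If they accept; recall of up to about 12 months for an early event |

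The gap is real but bounded. It covers the time from stopping to the next accepted visit.

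**2. How many could be affected?** The nearest stated figure is in the Sample size section: 80% completing, with a 95% interval of 72% to 86% at 140 participants. The exact binomial interval for 112/140 is 72.4% to 86.3%, so it reproduces. At the retention target, 0.20 × 140 = 28 participants may lack the 6-month executive-function assessment. The planning figure for the full trial is 10% dropout.

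**3. Illustration of size.** The article gives no event rate, so these inputs are assumptions:
- a = 10% of stayers have an event
- RR = 1, 2 or 3, the risk in stoppers relative to stayers
- c = share of affected stoppers whose event is captured by any route, before or after stopping
- d = share who stop, 20% or 10%

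True proportion = (1 − d)a + d·a·RR. Recorded proportion = (1 − d)a + d·a·RR·c. Missed share = d·RR(1 − c) / [(1 − d) + d·RR]. The base rate a cancels from the missed share.

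For d = 20%, RR = 3, c = 0: true = 0.08 + 0.06 = 14%; recorded = 8%; missed = 0.06/0.14 = 43%.

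| d | c | RR 1 | RR 2 | RR 3 |
|---|---|---|---|---|
| 20% | 0 | 20% | 33% | 43% |
| 20% | 0.5 | 10% | 17% | 21% |
| 20% | 0.8 | 4% | 7% | 9% |
| 10% | 0 | 10% | 18% | 25% |
| 10% | 0.5 | 5% | 9% | 13% |

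The c = 0 rows also discard events recorded at sessions before the person stopped, so they are upper bounds. With c = 1 nothing is missed.

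**4. Between arms.** Suppose d = 20% in EX and 10% in STRETCH, with RR = 2 and c = 0.5. The true proportions are 0.08 + 0.04 = 12% and 0.09 + 0.02 = 11%. The recorded proportions are 0.08 + 0.02 = 10% and 0.09 + 0.01 = 10%. The difference disappears. The unequal stopping is an assumption.

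**The case against.** The case against is substantial, and much of it stands.

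- **A reader might infer that someone who stops is never asked again.** The article does not support that. Withdrawn participants are invited to both follow-up time points, events are queried at each study visit, and Table 1 repeats medical history there.
- **A reader might infer that people who leave because of a harm are the least likely to be asked.** That is contradicted for those who report the harm: they are seen individually and, if judged unsafe to continue, followed weekly. Only those who leave without reporting fall outside.
- **An isolated missed session is not a lasting gap.** There are two group sessions a week, so the question usually returns within days.
- **The reason-for-leaving code should not be over-read.** It serves the retention outcome. Nothing says that a harm given as the reason goes ungraded, and the definition would include it.
- **The 20% figure is a tolerated limit.** It concerns one cognitive assessment, not loss of all contact.
- **The arms are time-matched and share the same rule.** Unequal loss is therefore possible but not shown.
- **This is a condensed article.** Call scripts and event forms may be in the full protocol, which is not shown.

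The last point does not dispose of the matter. The article states when participants are asked, and that rule is narrower than its own definition of what counts. An invitation is not an enquiry, and coordinator contact has no stated event question.

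**Conclusion.** The point holds in a limited form. For a participant who stops attending without having been judged unsafe, the article states no adverse-event enquiry until a visit that they may decline. Any events missed this way lower the recorded rate. How many are missed is unknown.

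The 10% to 21% range rests on 20% stopping, a risk ratio of 1 to 3 and half of the affected stoppers being captured. None of these inputs is an estimate from the trial; 20% is only the most non-completion the retention target allows. The 20% to 43% range is a ceiling. At 10% stopping and half captured, the range is 5% to 13%.

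It would be tempting to conclude that the decision to proceed would rest on a falsely favourable harm rate. The documents do not support that: the preset criteria in Objectives and hypothesis, and again in Analysis, are recruitment, adherence and retention. The effect on that decision is indirect. The point warrants a modest change to data collection and reporting and does not challenge the design.

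**What to change.** In the section on safety and monitoring procedures, add that the coordinator asks the same scripted adverse-event question as is used at sessions:

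1. when a participant has stopped attending;
2. when withdrawal is confirmed, alongside the medical or non-medical reason;
3. at the scheduled end of the intervention, for anyone not seen at the 6-month visit.

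Grade these events on the same CTCAE scale as all others. Report events by arm together with the number of participants asked through 6 months, so that a reader can see how complete the enquiry was.

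The cost is a little more coordinator time, since the article already describes phone availability and a withdrawal confirmation, and one extra line in the safety table. The reported event count may rise slightly. Trial status schedules the last intervention session for June 2025. If delivery has already ended, the number asked per arm can still be reported as far as session and visit records allow.

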### Analysis

Analysis of primary objectives related to feasibility outcomes will be descriptive. “Success” will be based on predetermined criteria outlined in “Objectives and hypothesis” which included: (1) Recruitment: ≥ 9 participants/month over 1.25 years; (2) Adherence: (a) ≥ 75% of Aerobic and Resistance Exercise (EX) sessions and ≥ 75% of Diet Counseling (DIET) sessions are completed; (b) improvement in diet quality at 6 months compared to baseline; (3) Retention: ≥ 80% of randomized participants complete the 6-month assessment of executive function. Overall, “success” will indicate that the protocol is adequately robust to proceed to a large RCT with small or no adaptations, and failure to meet these targets indicating a need for substantial change before proceeding. Preliminary analyses of feasibility outcomes will be conducted at the end of year 2 by an independent statistician when the first three waves complete their 6-month assessment. If the data support feasibility, the research team will apply for funding to roll directly into the definitive trial.

Full analyses will be conducted once all participants have completed their 12-month follow-up assessments. Analyses will explore whether feasibility outcomes vary by gender as research suggests that exercise and diet preferences vary by gender [45, 84]. Feasibility outcomes will be described among women and men, and among non-binary and other gender groups if possible. Analyses will also explore whether other demographics, geographical location, or technology access predict adherence. Characteristics of the participants who withdraw and reasons for withdrawal will be analyzed and intent-to-treat analyses will be used. Individuals who withdraw from the study will be invited to take part in post-intervention and 6-month post-intervention assessments and a sensitivity analysis will be completed. In addition, effect sizes for EX and DIET will be determined for the future, full-scale trial by gender. An analysis of effect sizes will be conducted from both intention-to-treat and per protocol analyses (to understand potential effectiveness in relation to adherence).

